### Genotyping

DNA will be extracted according to the standard protocol using the Qiagen DNeasy Blood & Tissue Kit. Genotyping for not less than 600,000 SNPs will be performed using whole-genome SNP-arrays of high coverage (tentatively, Illumina Infinium Global Screening Array). Each genotyping batch will be sampled using the block randomization method implemented in the OSAT R package [49] by Bioconductor (functions “setup.sample”, “setup.container”, “create.experiment.setup” and “get.experiment.setup” with case / control LDDD status, sex, age, availability of the disc tissue, place of birth, BMI, physical activity level, smoking status and date of blood sampling used as characteristics for optimization). The imputation procedure will be carried out using the Haplotype Reference Consortium [48] or a later reference panel.

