## Methods and analysis

### Study design and settings

This disease-oriented biobank to study lumbar disc degeneration will be recruited from two centers: the Priorov National Medical Research Center of Traumatology and Orthopedics (Priorov CITO), Moscow, Russia, and the Novosibirsk Research Institute of Traumatology and Orthopedics (NRITO), Novosibirsk, Russia. The study will be performed according to the Helsinki Declaration; the study protocol was approved by the Local Ethical Committee of the Novosibirsk Research Institute of Traumatology and Orthopedics (№034/20 dated 02 Oct 2020) and by the Local Ethical Committee of the Priorov National Medical Research Center of Traumatology and Orthopedics (№1/21 dated 25 Feb 2021). It will be conducted for a period of three years starting from 2021. Patients aged over 18 years with available MRI of the lumbar spine, who signed informed consent and met eligibility criteria, will be recruited. Clinical data and specimens will be collected in three visits as described in Table 1. At the first step, general information about a patient, his medical history and MRI scans of lumbar spine will be obtained. Patients’ biological material (whole blood and plasma) will be sampled in the centers at baseline. Then, from those patients, who will undergo a spine surgery during the treatment disc tissue samples will be gained. Eventually, postoperative clinical data will be collected from operated patients during the follow-up. Over three years, we expect to collect information and biological material from a total of 1,100 patients. A full schematic of the study is presented in Fig 1.

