**Fig 1 pone.0267384.g001:**
[figure not shown]
Patient selection. Sample size at various time-points of the project. Expected total sample size is 1,100. *Novosibirsk Research Institute of Traumatology and Orthopedics (NRITO) / Priorov National Medical Research Center of Traumatology and Orthopedics (Priorov CITO). **Conservative treatment.

**Table 1 pone.0267384.t001:** Scheduled procedures for clinical data and sample collection.

	Visit 1—Baseline	Visit 2—Day of surgery^1^	Visit 3–3 months after surgery^2^
Visit Window (±Days)			Day 90 ±14 days
Informed Consent	X		
Eligibility Criteria^3^	X		
Medical History	X		
Anamnesis Vitae	X		
Demographics	X		
Blood samples	X		
MRI	X		
ODI^4^	X		X
VAS^5^	X		X
Indications for surgery		X	
Surgical Procedure		X	
Intervertebral disc samples		X	
Adverse events/Serious adverse events	X	X	X

^1^only for patients subjected to surgery

^2^optional

^3^see Table 2 for details

^4^Oswestry Disability Index (ODI) scale

^5^Visual analogue scale (VAS) for back and leg pain.

All biological samples from NRITO will then be transported to the Institute of Cytology and Genetics (ICG), Novosibirsk, Russia, for long-term storage, further processing and omics profiling, including genotyping of blood samples and RNA sequencing of disc tissue. Priorov CITO will store the specimens on at their place.

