### Sample collection, transportation and storage

Samples collected in NRITO will be frozen at -40C (whole blood and plasma) or at -80C (disc samples) and then transferred to ICG for long-time storage at -80C. All biosamples from Priorov CITO will be frozen and stored on site at -80C.

Blood and plasma sampling: from each patient, 13 ml of peripheral venous blood will be collected into two BD Vacutainer 4-ml and 9-ml K2 EDTA tubes (or three 4-ml K2 EDTA tubes depending on availability). The tubes will be labeled with a patient’s unique code. During the first 30 min after blood collection, the 4-ml vacutainer with whole blood will be placed into a test tube rack and transported to the freezer to be stored at -40C. The 9-ml blood tube will be used for plasma extraction according to the plasma extraction protocol (see S2 File). Once the plasma has been extracted, the tubes with plasma will be labeled and placed into the freezer at -40C.

Eventually, all the tubes from NRITO will be transported to ICG in thermoboxes with cooling agents and then placed into freezers at -80C. Samples from Priorov CITO will be stored locally at -80C at once.

Collected plasma samples could be used for cell-free DNA, glycomics, proteomics and metabolomics analyses.

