### Data management

All data management and access procedures will be identical in both participating centers.

Each participant included in the study is assigned a unique code. Keys for these codes are saved in the locked storage of the internal hospital Electronic Data Capture (EDC) system, with access provided only for the curators of the study. All clinical data obtained from the patients are kept in the internal hospital EDC system accessible only by authorized researchers who are entering data into it. Information on who entered the data into the clinical database is available for viewing. During the study, internal monitoring will be conducted to maintain the quality of the study in accordance with the GCP principles. Participant and specimen codes are transferred to ICG along with the specimens from both clinical centers in an anonymous way.

Information on the physical location of specimens is kept with limited access only for curators of the study. Genotypes, transcriptomic data and data produced during their processing will be stored on a local server in ICG.

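### The balancing list for the omics samples leaves out recruiting centre although the two centres handle blood and plasma differently; crossing centre with case status is a cheap improvement

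*Protocol article*

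**What the plan says.** Patients "will be recruited from two centers" (Study design and settings). The Genotyping section optimises batches "with case / control LDDD status, sex, age, availability of the disc tissue, place of birth, BMI", and the list continues with "physical activity level, smoking status and date of blood sampling used as characteristics for optimization". That makes nine characteristics, without recruiting centre. The section on plasma N-glycosylation profiling calls for similar characteristics, and Total RNA profiling uses the set to decide which specimens are sequenced.

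The section Sample collection, transportation and storage sets handling that differs by centre. For the first centre it states: "Samples collected in NRITO will be frozen at -40C (whole blood and plasma) or at -80C (disc samples) and then transferred to ICG", the tubes travelling in cooled boxes before storage at -80C. By contrast, "Samples from Priorov CITO will be stored locally at -80C at once".

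The article is inconsistent on where Priorov CITO material goes. The text below Table 1 says "Priorov CITO will store the specimens on at their place" and links transport to ICG and profiling to NRITO samples. The collection and disc-sampling sections also keep Priorov CITO material on site. Data management, however, says that "specimen codes are transferred to ICG along with the specimens from both clinical centers".

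**The concern.** The list already includes date of blood sampling, so the plan accepts that a pre-analytical variable can be worth balancing. Centre marks the clearest pre-analytical divide that the article describes, and it is absent. Place of birth is at most a partial stand-in, because patients need not be treated where they were born.

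Plasma is the material for the glycan comparison between patients with and without LDDD. If one centre supplies a larger share of cases than of controls, a shift in glycan peaks caused by freezing or transport would appear as a disease difference. The centre mix among the assayed samples (at least 384 of 1,100, and about 40 discs) cannot be changed later without new assays.

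**Working it through.** The plan gives no figure on this point to reproduce. The check asks what the omission can do, and which remedy works.

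**1. Inputs.** From the article: two centres, at least 384 glycan profiles, about 40 RNA profiles, and the nine listed characteristics. Assumed: a handling shift of 0.5 SD on a glycan peak, equal numbers of cases and controls (192 and 192), and centre shares in cases and controls as shown below.

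**2. By hand.** Bias = handling shift × (centre share in cases − centre share in controls). SE = √(2/192) = 0.102 SD.

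- 30-point difference: 0.5 × 0.30 = 0.15 SD; 0.15/0.102 = 1.47; P(|Z + 1.47| > 1.96) = 0.31.
- 10-point difference: 0.5 × 0.10 = 0.05 SD; 0.05/0.102 = 0.49; P(|Z + 0.49| > 1.96) = about 0.08.
- Equal shares: bias 0, and the test keeps its 5% level.

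**3. By simulation.** No true disease effect, ordinary least squares, two-sided 5% test, 1,500 runs per row, n = 384, with 4 batches and a batch SD of 0.3 (both assumed).

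| Centre share, cases/controls | Batches balanced on | Bias, batch in model (SD) | False positives, batch in model | False positives, batch and centre in model |
|---|---|---|---|---|
| 50%/50% | case status | −0.005 | 4.2% | 5.0% |
| 50%/50% | case status and centre | 0.001 | 3.4% | 3.9% |
| 60%/50% | case status | 0.052 | 8.1% | 5.6% |
| 60%/50% | case status and centre | 0.051 | 7.1% | 5.8% |
| 70%/40% | case status | 0.145 | 27.4% | 4.8% |
| 70%/40% | case status and centre | 0.146 | 29.2% | 3.9% |

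The simulated 27–29% lies slightly below the hand figure of 31%. One reason is that the unmodelled centre shift adds to the residual variance, which the hand calculation ignores.

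**4. Reading the table.** Adding centre to the batch balancing leaves the bias where it was; 27.4% and 29.2% differ by no more than simulation error (standard error about 1.2 points each). A centre term in the model brings the rate back to about 5%, and so do equal centre shares.

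**5. RNA.** With n = 40, 2 batches and shares of 70%/40%, the bias is again about 0.15 SD. The false-positive rate with batch in the model is only 4.9–7.5%, because the standard error is much larger.

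**6. Which material is exposed.** The freezing contrast is explicit for blood and plasma. For discs, the Disc sampling section describes one liquid-nitrogen procedure without separating the centres, and both end at -80C; what remains is the transport of NRITO specimens. Nothing in the article indicates that freezer temperature changes genotype calls, and the GWAS uses quantitative degeneration scales, not the two-group test above.

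**The case against.** The strongest reply is that batch balancing serves another purpose: it keeps laboratory batch from being confused with disease. Case/control status heads the list, so that protection is already planned. A reader might infer that the omission by itself turns handling into a false disease effect. The article does not support this: the bias needs an unequal case mix by centre, which is not reported, and the table shows that balancing batches on centre would not cure it. This part of the reply stands. The list still matters where it also governs which specimens are profiled, as it does for RNA, because crossing centre with case status at that step does equalise the shares.

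A reader might also infer that no analysis could rescue the data if centre and batch coincided. That does not follow. A batch term would then also be a centre term, and the disease contrast within centre stays estimable provided each centre supplies both cases and controls.

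Two further replies stand. The article names no covariates for the glycan or expression models, but an analysis plan that is not shown may do so; that silence is not counted as an error here. And if only NRITO material is profiled, centre is constant and the issue disappears. The article leaves this open because its storage and transfer statements conflict.

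**Conclusion.** The concern holds in a limited form. An explicit list that reaches all three omics layers omits recruiting centre, while the same article sets different handling paths for blood and plasma by centre. If both centres are profiled and case mix differs between them, case/control comparisons could be biased, chiefly in the plasma glycome. Extending this to all the omics data would go too far, given step 6.

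The size is illustrative. With an assumed 0.5 SD shift and 384 samples, the false-positive rate is about 8% at a 10-point and about 27–31% at a 30-point difference in centre share; with equal shares there is no inflation. None of these inputs is a figure from the article. This is a cheap improvement to a stated rule, not a flaw that invalidates the design.

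**What to change.** - Add recruiting centre to the list in the Genotyping section, crossed with case/control status both when samples are selected for profiling and when they are allocated to batches. Carry this to the glycan and RNA sections.
- For RNA, cross centre with the degenerated/healthy-disc grouping that the expression analysis compares. The Discussion expects only 20 controls among operated patients, so in practice cases would be chosen to match the controls' centre split.
- Include centre as a covariate in the glycan and expression analyses. Batch balancing alone is not a substitute.
- Place samples from both centres in shared batches, so that centre and batch can be estimated separately.
- Reconcile the text below Table 1, the collection and storage section and the disc-sampling section with Data management on whether Priorov CITO specimens are shipped to ICG for profiling.

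The cost is one more allocation factor and one model degree of freedom, with no extra assays. Any Priorov CITO samples to be profiled must be available before plates are laid out.

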### Total plasma proteins N-glycosylation profiling

The plasma glycans profiling will be performed using the APTS glycan labelling kit (Genos) according to the standard protocol [49]. In short, plasma N-glycans are enzymatically released from proteins by PNGase F, fluorescently labeled with 2-aminobenzamide and cleaned up from the excess of reagents by hydrophilic interaction liquid chromatography solid phase extraction (HILIC-SPE) as described previously [50]. Fluorescently labeled and purified N-glycans are separated by HILIC on a Waters BEH Glycan chromatography column, 150 × 2.1 mm, 1.7 μm BEH particles, installed on an Acquity ultra-high-performance liquid chromatography (UHPLC) instrument (Waters, Milford, MA, USA) consisting of a quaternary solvent manager, a sample manager and a fluorescence detector set with excitation and emission wavelengths of 250 nm and 428 nm, respectively. Following chromatography conditions previously described in detail [50], glycan peaks (GPs)–quantitative measurements of glycan levels–are defined by manual integration of intensity peaks in the chromatograms. The abundance of N-glycans in each chromatographic peak is expressed as percentage area of the corresponding peak. Random allocation of the specimens will be carried out using the block randomization approach with the optimization characteristics similar to the genotyping procedure.

### Total RNA profiling

The intraoperative material will be homogenized using TissueLyzer II homogenator (QUAGEN) and total RNA will be extracted and converted to cDNA using a kit for the isolation of total RNA and microRNA from cells and tissues (Biolabmix, Russia) and the M-MuLV–RH First Strand cDNA Synthesis Kit (Biolabmix, Russia), respectively. The amount of extracted RNA and its quality will be estimated using Bioanalyzer 2100 (Agilent).

Total RNA sequencing will be performed using Illumina-HiSeq 4000 under the PE-protocol. A read length of up to 100 bp and a sequencing coverage of 20M are expected. Specimens will be randomly selected for sequencing utilizing the block randomization approach in order to maintain a uniform distribution of optimization characteristics set for genotyping batches. In total, not less than 40 samples will be profiled.

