#### Transcriptomic data analysis

The patient group with available intraoperative disc material (see Fig 1) could be divided into “cases” or “degenerated disc” (grades 4–5 of disc degeneration according to the Pfirrmann classification) and “controls” or “healthy disc” (grades 1–3 of disc degeneration according to the Pfirrmann classification) [44,60].

This division does not influence the scheme of patient recruiting or sample collection but plays a role in the transcriptomic data analysis. The groups will include following ICD-10 codes: M51.1 “Thoracic, thoracolumbar and lumbosacral intervertebral disc disorders with radiculopathy” (cases); M51.3, M51.8 “Other thoracic, thoracolumbar and lumbosacral intervertebral disc degeneration” (controls).

Transcriptomic data obtained in this study will be used for detection of genes differentially expressed in discs between cases and controls. In short, the gene expression data will be mapped [61] onto the reference genome and the quality of the reads will be recalibrated (“Picard Toolkit.” 2019. Broad Institute, GitHub Repository. http://broadinstitute.github.io/picard/; Broad Institute). Subsequently, aiming to reveal the transcriptomic differences in intervertebral discs tissue between cases and controls, we will count the reads and identify differentially expressed genes (DEGs) using the edgeR package [62]. To assess the statistical significance of the results, we will apply a Benjamini-Hochberg correction for multiple testing [63]. DEGs will be filtered by the q-value < 0.05 and divided into up- and down-regulated genes. Finally, the revealed DEGs will be functionally annotated with Gene Ontology terms.

The data will also be used to identify expression quantitative trait loci (eQTLs). We will perform an eQTL analysis of gene expression levels in intervertebral discs using the methodology described in [64]. Resulting regional association summary statistics will be used for gene prioritization.

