One more substantial strength of our study is the assessment of the disc degeneration grade by MRI scans, because this is the most accurate and precise method of DD diagnostics. In LDDD studies based on plain radiography [72] or CT [73], phenotype definition is rather subjective as these approaches provide only indirect evidence of disc degeneration such as disc height loss and osteophytes. Similarly, the use of self-reported questionnaires for LDDD identification [74] is not reliable enough. By contrast, the Pfirrmann grading system of disc degeneration used in the present study is based on MRI scans and estimates the main characteristics of DD by assessing the signal intensity and the height of the intervertebral disc: the more dehydrated the disc is, the more severe degenerative changes are in it [42].

This study has some limitations. First, the expected sample size is modest in comparison with national country-level biobanks or large prospective cohorts. The sample size of the present study is one-fourth as large as the one reported for meta-analysis of LDDD studies by Williams et al. [35]. This limitation is explained by funding, establishing the recruitment period of three years. Nonetheless, the expected number of disc tissue samples (~510) and their transcriptome profiles (~40) is comparable with other omics studies using disc specimens (proteome [33]: 7 cases / 7 controls; metabolome [39]: 60 cases / 21 controls; transcriptome [28]: 39 annulus fibrosus (AF) and 21 nucleus pulposus (NP) samples; [29]: 24 AF and 24 NP samples).

The next limitation of our study is an imbalance between patients with “healthy disc” and “degenerated disc” in the group of patients subjected to surgery. Obviously, patients with “healthy discs” are subjected to spinal surgery under specific circumstances. However, according to our protocol, we can still expect some controls in this group (in total, the expected number of controls is 20). In the groups not subjected to surgery, we expect a ratio between cases and controls to be closer to that in the general population.

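### The rule for choosing the 40 RNA-seq specimens does not block on the disc grade that defines cases and controls, so the planned expression contrast is not secured

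*Protocol article*

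**What the plan says.** **Selection.** Total RNA profiling says that "In total, not less than 40 samples will be profiled". On how they are chosen it says: "Specimens will be randomly selected for sequencing utilizing the block randomization approach in order to maintain a uniform distribution of optimization characteristics", and it identifies these characteristics as the ones used for the genotyping batches. The Genotyping section lists them: LDDD case/control status, sex, age, availability of disc tissue, place of birth, BMI, physical activity, smoking and date of blood sampling. Disc grade is not among them.

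**Contrast.** Transcriptomic data analysis splits patients with intraoperative disc material by Pfirrmann grade: 4–5 are cases (degenerated disc) and 1–3 are controls (healthy disc). It also attaches ICD-10 codes, M51.1 to cases and M51.3 and M51.8 to controls. Of this split it says "This division does not influence the scheme of patient recruiting or sample collection", and adds that it matters for the transcriptomic analysis. Differentially expressed genes are found with edgeR at a Benjamini-Hochberg q below 0.05.

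**Numbers.** The Discussion gives "the expected number of disc tissue samples (~510) and their transcriptome profiles (~40" and names the shortage of healthy discs among operated patients as a limitation: "we can still expect some controls in this group (in total, the expected number of controls is 20". No case/control split of the 40 profiles is stated anywhere.

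**The concern.** The selection rule was written for genotyping and carried over to RNA sequencing. For genotyping, LDDD case/control status is a sensible blocking variable, because the whole cohort includes patients seen for other reasons. Among disc donors it may hardly vary. Patient selection and expected sample size divides patients who attend for symptomatic LDDD into conservative treatment and surgery, and puts patients seen for other reasons in a separate group. Disc donors are therefore mostly symptomatic LDDD patients. Another listed characteristic, availability of disc tissue, is constant among donors. This suggests that the list was not adapted to the RNA-seq question.

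At stake is the only group comparison planned for the expression data. Controls are scarce in the pool. A rule that does not select on disc grade may sequence very few of them, although the biobank is expected to hold enough for a balanced comparison at the same sequencing cost.

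**Working it through.** The document states no power, effect size or case/control split for this analysis, so there is no figure of its own to reproduce. The check asks how many controls the rule would deliver under each reading, and how much that matters.

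**Inputs from the protocol article**
- Pool: about 510 disc samples (Discussion).
- Controls expected in the operated group: 20 (Discussion).
- Specimens sequenced: 40, stated as a minimum (Total RNA profiling).

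**Assumptions, not in the document**
- A standardised difference of 1.5 SD for a gene.
- A two-sided per-gene p of 0.001, standing in for the threshold that q < 0.05 would imply.
- A two-sample t-test as a stand-in for edgeR.

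**Step 1. Controls sequenced if selection does not act on disc grade**

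Share of controls in the pool: 20/510 = 3.9%.

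Expected controls among 40: 40 × 20/510 = 1.57.

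If the draw is random with respect to grade, the count is hypergeometric (pool 510, controls 20, draw 40):

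| Controls among 40 | Probability |
|---|---|
| 0 | 0.19 |
| 1 or fewer | 0.52 |
| 2 or fewer | 0.80 |
| 3 or fewer | 0.94 |

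The expected count is the same, about 1.6, if blocking does act on grade but only keeps the sequenced set in proportion to the pool.

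**Step 2. Controls sequenced if selection is equalised on disc grade**

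Half of 40 is 20, which the 20 expected controls just allow. The split would be up to 20 v 20.

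**Step 3. What the split does to the comparison**

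For a controls and b cases, the information on a mean difference is proportional to ab/(a + b). The noncentrality is 1.5 × √[ab/(a + b)], with 38 degrees of freedom and a critical t of 3.566.

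| Controls v cases | ab/(a + b) | Noncentrality | Power |
|---|---|---|---|
| 2 v 38 | 76/40 = 1.9 | 2.07 | 9% |
| 10 v 30 | 300/40 = 7.5 | 4.11 | 70% |
| 20 v 20 | 400/40 = 10 | 4.74 | 87% |

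A 2 v 38 split carries 1.9/10 = 19% of the information of 20 v 20; a 10 v 30 split carries 75%. A normal approximation gives somewhat higher powers (11%, 79% and 93%) in the same order.

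**The case against.** The strongest answer is that the draw is not a simple random one. It is blocked, and LDDD case/control status is the first characteristic on the list. The hypergeometric model ignores case status, so it applies only if that variable does not act on the contrast. The document also uses the words cases and controls for operated patients, in Transcriptomic data analysis and again in the Discussion. The blocking variable could therefore be meant as the Pfirrmann-based group. On that reading, with uniform taken as equal numbers, 20 expected controls and about 40 profiles fit a 20 v 20 design.

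This stands to the extent that a balanced draw is possible and may be intended. It does not settle the matter. The Genotyping section does not define its status variable by disc grade. Equal numbers at every level of nine characteristics cannot be had in 40 specimens, so uniform may equally mean similar in composition to the pool. The Discussion places the 20 controls in the whole operated group and gives no split for the sequenced set.

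A reader might infer that only one or two controls will be sequenced and that the expression analysis is bound to fail. The document does not support that. The low count follows from one reading of an unclear rule, and an intermediate split such as 10 v 30 would keep most of the information.

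Three further points are fair. The imbalance is disclosed as a limitation. The main aim is the biobank, and these analyses are presented as designs of further studies. The statement that the split leaves recruitment and sample collection unaffected does not itself decide which stored discs are sequenced.

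**Conclusion.** The selection rule, as written, does not secure the case-control contrast that it is meant to serve. The variable that defines the contrast is absent from the blocking list, and the nearest listed variable may vary little among disc donors. Depending on the reading, the rule delivers anything from about 1.6 expected controls (19% chance of none) to 20 of the 40.

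The control counts rest on the document's approximate figures of 510, 20 and 40. The powers rest on the assumed effect, threshold and t-test, and serve only to rank the splits. This is an inexpensive improvement to an ambiguous rule, not proof that the analysis cannot work. It should be settled before specimens are chosen for sequencing.

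**What to change.** In Total RNA profiling, state that specimens are selected for sequencing stratified on the Pfirrmann grade of the resected disc. Take all available grade 1–3 discs up to about 20. Fill the remainder of the 40 with grade 4–5 discs, chosen by the existing block randomisation on the other characteristics. State the intended numbers of cases and controls.

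The change is one of wording, and the number of libraries stays at 40. The downside is small: the sequenced set would no longer represent all operated patients, so descriptive statements about that population should not be drawn from it without allowing for the selection.
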